## Abstract

**Background:**

Acute care nurse practitioners (ACNPs) in postoperative cardiac surgery settings provide significant benefits to patients and organizations. Recent studies have suggested that ACNPs increase the level of adherence to best-practice guidelines by interprofessional teams. It is however, unknown whether interprofessional teams with ACNP are associated with higher levels of adherence to best-practice guidelines compared to interprofessional teams without ACNPs. Furthermore, no extraction tool is available to measure the level of adherence to best-practice guidelines by interprofessional teams in postoperative cardiac surgery settings. This project aims to measure and examine the level of adherence to best-practice guidelines of interprofessional teams with and without ACNPs in a postoperative cardiac surgery setting in Québec, Canada.

**Methods:**

A retrospective observational study will be conducted of 300 patients hospitalized between January 1, 2019 and January 31, 2020 in a postoperative cardiac surgery unit in Québec, Canada. Data will be collected from patient health records and electronic databases. An extraction tool will be developed based on systematic review of the literature, and will include best-practice guidelines and confounding variables related to patient and interprofessional teams’ characteristics. Content and criterion validation, and a pilot-test will be conducted for the development of the tool. A multivariate linear regression model will be developed and adjusted for confounding variables to examine the association between interprofessional teams with and without ACNPs, and level of adherence to best-practice guidelines by those teams.

**Discussion:**

This project represents the first study to measure and examine the level of adherence to best-practice guidelines by interprofessional teams with and without ACNPs in a postoperative cardiac surgery setting. The findings of this project will generate empirical data focusing on the contribution of ACNPs within interprofessional teams, and ultimately enhance the delivery of high quality and evidence-based care for patients and families.

## Background

Cardiac surgeries are one of the leading types of surgical procedures performed internationally. In 2017, approximately one million patients underwent cardiac surgery, the majority of whom reside in developed nations [1]. In 2018, the Society of Thoracic Surgeons (STS) reported 287,872 cardiac surgeries and procedures performed in the United States [2]. In Canada, 42,989 coronary artery bypass grafts (CABG) and 7,186 valve repairs were performed between 2013 and 2016 [3, 4]. In 2014, Germany had the highest rate of coronary revascularization procedures among the European union with 453 procedures per 100,000 population, followed by Austria (324 procedures per 100,000 population), Croatia (324 procedures per 100,000 population), and Lithuania (319 procedures per 100,000 population) [1].

In the postoperative phase after cardiac surgery, many patients are at high risk of developing adverse events and postoperative complications such as myocardial infarction and wound infection [5]. These complications are associated with higher risk of mortality and the development of comorbidities (e.g., heart failure), as well as a decrease in well-being and quality of life of patients and families [6]. For healthcare organizations, adverse events and postoperative complications are associated with a longer length of stay at the hospital, higher rates of readmission in intensive care units, higher rates of surgical re-exploration, and increased costs [7, 8].

To prevent the risk of adverse events and postoperative complications for patients and families, healthcare organizations and research teams internationally have developed best-practice guidelines [7, 9]. Best-practice guidelines are defined as evidence-based practice aimed to ensure the performance of interprofessional teams, to enhance the quality and safety of the care given to patients and families. In postoperative cardiac surgery settings, best-practice guidelines related to pharmacotherapy, laboratory tests, clinical indicators, and lifestyle promotion (e.g., diet, cardiac rehabilitation) have been developed and implemented in healthcare organizations [2].

A consensus in the literature supports the importance of a high level of adherence by interprofessional teams to best-practice guidelines to ensure their efficacy [7, 10]. Adherence to best-practice guidelines is defined as the achievement of the guideline, as well as the associated interventions performed by clinicians [11]. In surgical settings (e.g., neurosurgery, orthopedic surgery) international research teams [12–15] have developed composite scores to examine the level of adherence to best-practice guidelines by interprofessional teams. Their findings suggest that a higher level of adherence is associated with a higher quality of care given to patients and families.

In postoperative cardiac surgery settings, recent studies [5, 16] identified a significant association between a high level of adherence to best-practice guidelines by interprofessional teams and a lower risk of postoperative complications and adverse events for patients. Other studies [17] have shown a significant association between a lower level of adherence to best-practice guidelines by interprofessional teams and a higher risk of postoperative complications and adverse events for patients. Larrazet et al. (2014) conducted a longitudinal study of 144 patients who died after cardiac surgery. The authors identified a significant association between a lack of adherence to best-practice guidelines by interprofessional teams, and a higher risk of mortality, highlighting the importance of the high adherence to best-practice guidelines by interprofessional teams [17].

Internationally, there is variability in the scope of practice and level of autonomy of acute care nurse practitioners (ACNP) [18, 19]. Recent studies have examined the practice of nurse practitioners (NP) within primary and acute care settings and suggest that their practice could increase the level of adherence to best-practice guidelines by interprofessional teams [18, 19]. NP’s evidence-based practice is believed to support care providers’ adherence to best-practice guidelines within the areas of pharmacotherapy, clinical indicators, and lifestyle promotion. NPs also enhance collaboration and communication among teams’ members and facilitate continuity of care, contributing to the higher adherence to best-practice guidelines by interprofessional teams [18, 20].

Based on the International Council of Nurses guidelines, the NP is an advanced practice nursing role, based on a graduate or postgraduate education and an in-depth nursing and clinical expertise (e.g., prescription of the pharmacotherapy, diagnosis, etc.) [21–23]. In postoperative cardiac surgery, ACNP have been implemented in interprofessional teams and performed activities such as the clinical and psychosocial assessment of patients, the prescription and management of pharmacotherapy, laboratory tests and clinical interventions, lifestyle promotion, teaching of coping strategies, preparation for hospital discharge, and the management of consultations and external resources [24]. International research teams [23, 25] have examined the practice of ACNP within postoperative cardiac surgery settings. They identified significant associations between the ACNP’ practice and higher patient satisfaction during their hospital stay, higher rates of patients participating in cardiac rehabilitation programs, and reduced length of stay at the hospital after the cardiac surgery. In contrast, other research teams [21, 26] did not identify significant associations between ACNP practice and patient and organizational outcomes within postoperative cardiac surgery settings. More specifically, the authors suggested that the difficulty of recruiting participants, the high attrition rate, the small sample sizes, and the inability to adjust the data analysis for confounding variables related to the patient and interprofessional teams’ characteristics were important limits contributing to the non-significant findings [21, 26].

Systematic reviews of randomized controlled trials (RCT) [21, 23] have been conducted to understand the inconsistent findings in the current literature. These systematic reviews have identified three important limits contributing to the inconsistent findings of the current literature. Firstly, although several RCTs have focussed on the efficacy of ACNPs for patients and healthcare organizations, less attention has been paid to the efficacy of these providers for interprofessional teams. The qualitative study by Reich et al. (2018) suggested that the implementation of ACNPs within interprofessional teams increases the level of adherence of those teams to best-practice guidelines in postoperative cardiac surgery settings, and represents an underlying factor contributing to the efficacy of these teams [19]. However, these propositions have not been subjected to statistical validation, thus it is unknown if interprofessional teams with ACNP are associated with higher levels of adherence to best-practice guidelines, compared to interprofessional teams without ACNP. Additionally, to date no validated extraction tool to measure the level of adherence to best-practice guidelines of interprofessional teams with and without ACNPs in postoperative cardiac surgery has been located.

Secondly, systematic reviews of randomised controlled trials (RCTs) have revealed that many variables (e.g., severity of illness) influence the effect of ACNP practice on patient and organizational outcomes in postoperative cardiac surgery settings. These variables have not been adequately controlled in current RCTs [21, 23]. Methodological limits of the existing RCTs, such as the small sample size and high attrition rate, limit the capacity of research teams to develop robust multivariate statistical models adjusted for confounding variables related to patient, interprofessional teams, and organizational characteristics [21, 23]. Interestingly, retrospective observational studies have been shown to be a relevant alternative to examine the association between ACNP and patient and organizational outcomes in postoperative cardiac surgery settings. Existing studies [27–30] have used retrospective patient cohorts to develop models adjusted for confounding variables. These studies [6, 27–29] have identified significant associations between interprofessional teams with ACNPs and lower mortality risk and decreased costs in postoperative cardiac surgery settings.

Thirdly, the majority of the RCTs focus on NP practice within primary care settings (e.g., in-home care, rehabilitation clinic) after the cardiac surgery. Less attention has been paid to ACNP practice in acute care settings; however, within these settings, ACNPs work in collaboration with cardiac surgeons, nursing teams, rehabilitation teams, social workers, and other members of interprofessional teams to ensure the patient’s optimal recovery, and reduce adverse events and postoperative complications. For patients and families, hospitalization in acute care represents a crucial phase of postoperative recovery associated with several physical, psychosocial, and emotional stressors [30]. Additional studies are needed to substantiate the contribution of ACNPs in interprofessional teams within acute care settings, and identify the benefits of their practice for patients, families, interprofessional teams, and healthcare organizations. The aim of this project is to measure and examine the level of adherence to best-practice guidelines of interprofessional teams with and without ACNPs in an acute postoperative cardiac surgery unit in Québec, Canada.

### Study hypothesis and objectives

The hypothesis of this study is:

H1: It is hypothesized that interprofessional teams with ACNP are associated with a higher level of adherence to best-practice guidelines compared to interprofessional teams without ACNP, after controlling for the patient and interprofessional team characteristics.

The objectives of this study are as follows:

Develop and pilot-test an extraction tool to measure the level of adherence to best-practice guidelines of interprofessional teams within a postoperative cardiac surgery setting.Describe the patient and interprofessional teams’ characteristics, as well as the level of adherence to best-practice guidelines, of patients under the care of interprofessional teams with and without ACNPs.Examine the association between interprofessional teams with ACNPs and the level of adherence to best-practice guidelines, compared to interprofessional teams without ACNPs, after adjusting for patient and interprofessional team characteristics in postoperative cardiac surgery.

## Methods and design

### Study design

A retrospective observational study [31, 32] will be conducted. De-identified data will be extracted from the University healthcare centre (UHC) data warehouse and the patient health records to assemble the retrospective cohort of patients, and conduct the data collection. Ethics approval was obtained from the McGill University Health Centre Research Ethics Board on September 15, 2021 (IPSSA chirurgie cardiaque/2022-8094). The *Strengthening the Reporting of Observational Studies in Epidemiology (STROBE) Statement*: *Guidelines for Reporting Observational Studies* [32] will be used as a framework to conduct this project (S1 Appendix).

### Study setting

This study will be conducted at a UHC in Québec, Canada, where approximately 1,000 cardiac surgeries are performed annually in a 36-bed postoperative cardiac surgery unit.

After cardiac surgery, patients are admitted to the intensive care unit (ICU), and are under the care of ICU teams. At the time of data collection, the ICU teams in Québec, Canada did not include ACNPs. On average, patients are hospitalized for 24 hours in the ICU before being transferred to the postoperative cardiac surgery unit. Patients readmitted to the ICU are under the care of ICU teams.

Upon admission to the postoperative cardiac surgery unit, patients are assigned to the care of interprofessional teams with or without ACNPs. Team assignment depends on the current workload of each team, and the availability of the beds in the unit. Interprofessional teams with ACNPs are responsible for 16 of the unit’s beds (44%) and interprofessional teams without ACNP are assigned 20 of the unit’s beds (56%). Patients are followed by their respective teams from their admission to the cardiac surgery unit until hospital discharge or death. On average, the length of stay at the hospital after the surgery ranges from 9 to 11 days [33].

Interprofessional teams with and without ACNPs include the following: cardiac surgeons and physician residents, nursing teams, skin and wound care specialists, physiotherapists, nutritionists, respiratory therapists, social workers, and other medical specialists. Interprofessional teams with and without ACNPs ensure daily follow-up of patients, assessment of the patient’s clinical and psychosocial condition, management of pharmacotherapy, clinical interventions, prescribing and monitoring of laboratory tests, lifestyle promotion, and the preparation of patients for hospital discharge.

### The practice of acute care nurse practitioners in the postoperative cardiac surgery unit

Since 2017, seven ACNPs practice in postoperative cardiac surgery, based on a monthly rotation system. Two ACNPs simultaneously practice within interprofessional teams and collaborate with other clinicians to ensure the daily follow-up of the patients after cardiac surgery. In addition to the activities described above, the ACNPs also teache coping strategies, lifestyle promotion, cardiac rehabilitation, preparation of the patients and families for the in-home recovery after discharge. The ACNPs support the preparation for hospital discharge (e.g., prescription of the patient medication after discharge, summary for the family physician, etc.) [34].

### Study population and sample

A retrospective cohort of patients will be assembled with patients hospitalized at the postoperative cardiac surgery unit between January 1, 2019, and January 31, 2020. This timeframe will avoid the recruitment of patients during the COVID-19 pandemic, a window of time during which the practice of ACNPs within the unit was inconsistent. Patients will be selected, based on three inclusion criteria: 1) patient admitted with a diagnosis of coronary artery bypass graft (CABG) and/or valve repair, 2) patient age is over 18 years old, and 3) patient has been hospitalized for at least 24 hours in the postoperative cardiac surgery unit. The minimum 24-hour criteria will allow the research team to examine the hospitalization of the patient in the postoperative cardiac surgery unit, which is the setting where ACNPs practice in Québec [35]. Patients will be identified from the electronic databases of the UHC and the diagnostic codes of the Canadian Institute for Health Information [36] (S2 Appendix).

A sample size calculation was conducted in G*power [37]. This project will include 15 variables, including one independent variable, one dependent variable, and 13 confounding variables. The variables selected for this project are described in the next section. To perform one multivariate linear regression model and detect an effect size of *f*^*2*^ = 0.15 with a power of 0.80 and a standard error of 5%, a minimum sample size of 183 patients was estimated.

A total of 300 patients will be selected, based on the sample size calculation and an over-estimation of at least 20%, to consider the risk of error from the presence of missing data and incomplete patient health records [38, 39]. A systematic random selection of 150 patients under the care of interprofessional teams with ACNP will be conducted and matched with 150 patients under the care of interprofessional teams without ACNP. Three criteria [40–43] will be used simultaneously to match each pair (1:1): 1) age (i.e., a five-year gap will be tolerated) 2) sex, and 3) type of cardiac surgery (i.e., CABG, valve repair, or CABG/valve repair).

Patients will be followed from their admission to the ICU after the cardiac surgery, until the occurrence of the following events, whichever occurs first: 1) discharge from the hospital, 2) death, or 3) the cumulation of 14-days in hospital after the surgery. The 14-days’ timeframe will allow the research team to capture the acute phase of the patient’s hospitalization after the cardiac surgery [33]. The total length of stay for patients hospitalized longer than 14-days will be measured.

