#### Variables influencing the effect of acute care nurse practitioner practice related to interprofessional teams’ characteristics

Two influencing variables related to interprofessional teams’ characteristics will be measured. First, the cardiac surgeon who performed the surgery and ensured the follow-up of the patient’s recovery will be noted. A confidential code will be created for each surgeon practising in the UHC. Second, a discrete variable will be created to measure the number of consultations conducted by clinicians from different professional groups (e.g., nutrition, rehabilitation team) during the patient’s hospitalization in the postoperative cardiac surgery unit. A categorical descriptive variable will be created to measure each clinician’s professional group, including the following: 1) rehabilitation team (e.g., physical therapist, occupational therapist), 2) respiratory therapist, 3) social worker, 4) skin and wound care therapist, 5) nutritionist, and 6) speciality consultation (e.g., internal medicine, nephrology).

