A multivariate linear regression model will be developed to examine the association between interprofessional teams with and without ACNPs and the level of adherence to best-practice guidelines [63–65]. An examination of the distribution of the data will be performed. In the case of an abnormal distribution of the data, a transformation will be conducted to adjust the statistical model based on the observed data. The independent variables will include the interprofessional teams with and without ACNPs, as well confounding variables. A correlation matrix will be developed, and tolerance value lower than 0.2 and a variance inflation factor (VIF) value higher than 5 will be used to identify multicollinearity between independent variables [63–65]. Independent variables with multicollinearity will be removed one at the time and a new regression will be calculated. The dependent variable of the regression model will be the average composite score (%) of the level of adherence to best-practice guidelines. Statistical significance will be based on a *p*-value of 0.05. Sensitivity analysis will be conducted based on a selection of confounding variables related to the characteristics of the patient (e.g., length of stay, ICU readmission). The selection of these confounding variables will be based on the observed data and descriptive analysis. The residual analysis and the analysis of the R^2^ will be conducted to assess the goodness-of-fit of the multivariate linear regression model.

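### The minimum of 183 patients does not follow from the stated inputs (135 to 139 for the whole model, 55 for one coefficient), and the protocol does not say which effect f² = 0.15 describes

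*Protocol article*

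**What the plan says.** Under Study population and sample, the protocol article names the software ("A sample size calculation was conducted in G*power") and counts the model: "This project will include 15 variables, including one independent variable, one dependent variable, and 13 confounding variables". That makes 14 predictors and one outcome. The aim of the calculation is to "detect an effect size of *f*^*2*^ = 0.15 with a power of 0.80", and the result is given as "with a power of 0.80 and a standard error of 5%, a minimum sample size of 183 patients was estimated". The sample is then set at 300 (150 per team type, matched 1:1), citing an over-estimation of at least 20% for missing data and incomplete records.

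H1, under Study hypothesis and objectives, is that "interprofessional teams with ACNP are associated with a higher level of adherence to best-practice guidelines compared to interprofessional teams without ACNP", after control for patient and team characteristics. Data analysis, Objective 3, sets the significance level of the regression at 0.05. Among the confounders, type of surgery has three categories, and for surgeon "A confidential code will be created for each surgeon practising in the UHC". The number of surgeons is not given.

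**The concern.** The paragraph gives effect size, power, error rate, number of variables and software, so a reader should be able to recover the minimum. If it cannot be recovered, the stated pairing of size and power is wrong or an input has gone unreported.

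The second issue is what the effect size describes. H1 concerns one adjusted coefficient. The paragraph speaks of performing one regression model and detecting f² = 0.15, supported by a count of all variables. It names no test and does not say whether 0.15 is the f² of the whole model or the partial f² of the team term. These are very different assumptions, and only the second bears on H1. As written, the protocol states no ACNP difference that the study is designed to detect.

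**Working it through.** **Inputs.** f² = 0.15, power 0.80 and α = 0.05 (Study population and sample; the α is confirmed under Data analysis, Objective 3). Predictors p = 1 + 13 = 14, or 15 if the outcome is counted by mistake.

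**Method.** Fixed-model regression F test. The noncentrality is λ = f² × N, the numerator degrees of freedom are u (terms tested), and the denominator degrees of freedom are N − p − 1. The required N is the smallest with power of at least 0.80.

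**Attempt to reproduce 183.**

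| Test | Terms tested / in model | Required N | λ at that N | df |
|---|---|---|---|---|
| Whole model | 14 / 14 | 135 | 20.25 | 14, 120 |
| Whole model | 15 / 15 | 139 | 20.85 | 15, 123 |
| One coefficient, two-sided | 1 / 14 | 55 | 8.25 | 1, 40 |

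None gives 183. The excess is 183/135 = 1.36 or 183/139 = 1.32, that is 32% to 36% too high for the whole-model test. At N = 183 with 14 predictors (λ = 27.45; df 14, 168), whole-model power is 0.93. One-coefficient power at the same f² is 0.999.

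**Could inflation explain it?** Allowing for 20% loss, 135/0.8 gives 169 and 139/0.8 gives 174. Allowing for 25% gives 180 and 186. None is 183, and the paragraph presents 183 as the minimum, with the over-estimation applied afterwards to reach 300.

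**Could the number of terms explain it?** At the stated f², α and power, 28 terms need 181 and 29 terms need 184, so no whole-model count returns 183.

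**Why the target of f² matters.**
- Whole-model reading: if ACNP has no effect but the covariates carry f² = 0.15, the whole-model test still rejects with probability 0.93 at N = 183 and 0.998 at N = 300. Power on this reading says nothing about H1.
- ACNP-term reading: for a balanced binary exposure uncorrelated with the covariates, d = 2√f² = 2√0.15 = 0.77 residual SD.

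**What the planned sample can detect for the team term** (u = 1, p = 14, two-sided 5%, power 0.80):
- N = 300: partial f² = 0.0263, so d = 2√0.0263 = 0.32 SD.
- N = 300 × 0.8 = 240: partial f² = 0.0330, so d = 2√0.0330 = 0.36 SD.

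The SD values assume balance and no correlation between team and covariates. In general d = 2√(f² × VIF), where VIF is the variance inflation factor of the team term. With VIF = 2 as an illustration, 0.32 × √2 gives about 0.46 SD at N = 300. No clustering allowance is included.

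**The case against.** The strongest defence has three parts.

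First, an unreported but legitimate count of terms may lie behind 183. Coding surgery type as two dummy terms and surgeon as one fewer than the number of surgeons would give 28 to 29 terms if there were about 15 to 16 surgeons, and hence 181 to 184. This is an assumption, because no surgeon count is given. It also conflicts with the paragraph's own count of 15 variables and still does not return 183. It shows only that the figure may come from an input that was not reported.

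Second, the error does no harm to power. Both 183 and 300 exceed what f² = 0.15 requires on either reading. This stands in full.

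Third, a reader might infer that 183 came from a whole-model test and that the study is therefore powered for the wrong hypothesis. The document does not support this. It names no test, 183 reproduces under neither test, and nothing under Data analysis says that H1 will be judged by the overall F test. What can be said is that the target of f² is not stated. Nor can 183 be traced to particular alternative settings: 13 predictors at α = 0.025 and power 0.90 return 183 exactly, but only by altering stated inputs, and other altered combinations come within a patient or two.

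**Conclusion.** The stated minimum is wrong on the inputs reported: 183 against 135 to 139 (whole model) or 55 (one coefficient), with whole-model power of about 0.93 at 183 rather than 0.80. This rests on the fixed-model F test and on reading the 15 variables as 14 predictors, or at most 15. Separately, f² = 0.15 is not tied to the ACNP term that H1 tests.

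This is a fault of reporting and reproducibility, and it should be corrected. It is not a shortage of power at f² = 0.15, and the planned 300 need not change. A reader might also infer that a null result could not be interpreted. That goes too far: the confidence interval of the adjusted team coefficient would still be informative. What is missing is a planned detectable ACNP difference against which to read it.

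**What to change.** Keep 300 and replace the 183 statement with the calculation for the coefficient that H1 concerns (increase in R², one tested predictor). Suggested wording:

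*With 14 predictors in the model, 300 patients (240 if 20% of records are unusable) give 80% power at a two-sided type I error of 5% to detect a partial f² of about 0.026 (0.033) for team type. This corresponds to about 0.32 (0.36) residual SD between teams if team is balanced and uncorrelated with the covariates. The detectable difference grows by the square root of the team term's VIF (about 0.46 SD at 300 patients if VIF = 2). No allowance for clustering is included.*

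Replace 14 with the actual number of terms after dummy coding surgeon and surgery type, and rerun. The one-coefficient result should move little, because only the denominator degrees of freedom change (for example 300 − 14 − 1 = 285 against 300 − 29 − 1 = 270). Say why a difference of this size matters, since a figure solved from a fixed N does not show that. Write 'type I error' for 'standard error'.

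The cost is rewording one paragraph, with no added patients and no change to the analysis.
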